### Statistical analysis

The normality of the primary variables will be assessed using the Shapiro-Wilk test, and homogeneity of variances will be evaluated using Levene’s test. If normality is satisfied, a repeated measures ANOVA will be performed to examine the main effects of time, group, and their interaction. Mauchly’s test for sphericity will be conducted, and if violated, the Greenhouse-Geisser correction will be applied. If the normality assumption is violated, non-parametric alternatives will be implemented. The Kruskal-Wallis test will be used for between-group comparisons at each time point, while the Friedman test will be applied for within-group repeated measures. To adjust for multiple comparisons, Bonferroni correction will be applied as needed to control for Type I error. If significant interaction effects are observed in the repeated measures analysis, post-hoc tests will be conducted. For parametric statistics, paired t-tests will be used to compare within-group differences over time, and independent t-tests will be performed to compare mean differences between groups at the same time points. For non-parametric statistics, the Mann-Whitney U test will be used to compare two groups at a specific time point, and the Wilcoxon signed-rank test will be employed to analyze within-group differences between two time points.

All data collected in this study will be analyzed using SPSS 26 statistical software. The five subscales and total score of the Wechsler assessment will be analyzed separately. Since multiple comparisons will be made, a multiple comparisons issue may arise. To address this, the Bonferroni correction will be applied, setting the significance level to 0.0167. For other variables, the significance level will be set to 0.05 for analysis.

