## Materials and methods

### Study design

This prospective randomized controlled intervention received approval from the Institutional Review Board of Incheon St. Mary’s Hospital (OC24FISI0032) on April 22, 2024. The protocol complies with the Helsinki Declaration and Good Clinical Practice guidelines. Participants will be divided into three groups: intervention group 1 (PA and PST), intervention group 2 (PA), and a control group (no intervention).

Initially, the two intervention groups will be categorized by age. We will randomly assign 18 children and their parents to each group, resulting in 72 participants, using a random number generator (version 1.1). The control group will consist of 18 children and their parents (36 participants) selected from those unable to participate in the interventions but who could complete the assessments. Therefore, the total number of participants across all groups will be 54 children, 54 parents, and 108 individuals.

To enhance the robustness of the analysis and mitigate potential biases from participant dropout, an intention-to-treat (ITT) approach will be implemented. All randomized participants will be analyzed regardless of intervention adherence. Missing data will be managed using multiple imputation methods to preserve data integrity and minimize bias. Additionally, sensitivity analyses will be conducted to evaluate the potential impact of missing data on the study outcomes.

All participants in this study will continue to receive their existing medication treatments throughout the intervention period. Before proceeding with the assessments and interventions, the children and their parents will provide written informed consent. Recruitment and data collection began on May 31, 2024 and is expected to end on February 28, 2025. Data collection and results are expected to be completed by September 30, 2025. Details of the research procedure are presented in Fig 1.

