### Sample size

The sample size for this study was determined through statistical analysis using the G*Power 3.1 program. Based on the data analysis method, the test family was set to F-tests, and the statistical test was designated as ANOVA: repeated measures, within-between interaction. The effect size was determined according to Cohen’s method [26] and was set to 0.25, based on previous studies [27–29]. Initially, the significance level (α) was set at 0.05 for the sample size calculation. However, to account for multiple comparisons, the Bonferroni correction was applied, adjusting the per-comparison significance level to α = 0.0167. The statistical power (1-β) was set at 0.80, the number of groups at three, and the number of repeated measurements at three. Consequently, the required sample size was recalculated to be 45 participants (15 per group). To account for potential attrition, a 20% dropout rate was considered, based on rates observed in previous studies [30–32]. Therefore, the final total sample size was 54 participants, with 18 participants allocated to each group.

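### The between-group comparisons at each visit ignore the baseline score already collected, and the group main effect averages it in; both give up precision in a trial with 15 to 18 children per arm

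*Protocol article*

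**What the plan says.** Under Statistical analysis, if normality holds, "a repeated measures ANOVA will be performed to examine the main effects of time, group, and their interaction". No covariate is named. If the interaction is significant, "independent t-tests will be performed to compare mean differences between groups at the same time points"; the non-parametric branch uses Mann-Whitney tests at a given visit.

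Under Outcome measures, every measure except the K-WISC-V is taken at baseline, at about three months and at about six months. The K-WISC-V is taken twice. Baseline is therefore the first of three levels of the time factor.

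The sample size was computed for "ANOVA: repeated measures, within-between interaction", with the correction "adjusting the per-comparison significance level to α = 0.0167". The analysis section keeps 0.0167 for the Wechsler scores and then states: "For other variables, the significance level will be set to 0.05 for analysis".

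Under Study design, "Initially, the two intervention groups will be categorized by age", followed by random assignment to those two groups. The control group is selected from families who cannot take part in the interventions. On incomplete records, "Missing data will be managed using multiple imputation methods to preserve data integrity and minimize bias".

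**The concern.** Treatment cannot affect the baseline score, but that score predicts the later ones. The planned analysis uses it poorly in two places. The group main effect averages the baseline visit in with the two visits where an effect can appear. The per-visit t-tests and Mann-Whitney tests, which yield the group differences a reader will look for, leave baseline out.

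The comparison that rests on randomisation, IG 1 against IG 2, has 18 children per arm enrolled and 15 planned as evaluable. At that size, wider intervals could decide whether a real difference between the combined programme and physical activity alone is detected. The information needed to narrow them is already collected.

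**Working it through.** **Inputs.** From Sample size: f = 0.25, alpha 0.0167, power 0.80, three groups, three measurements, 45 evaluable (15 per group), 54 enrolled. From Statistical analysis: alpha 0.05 for non-Wechsler outcomes. Assumed, because not stated: two-sided tests; unit SD; the same correlation ρ between any two visits (0.3, 0.5, 0.7); an effect of 0.8 SD.

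**1. The plan's own figure.** For the within-between interaction, λ = f²·N·m/(1−ρ). With ρ = 0.5 and sphericity, λ = 0.0625 × 45 × 3 / 0.5 = 16.875 on 4 and (45−3) × 2 = 84 degrees of freedom. Power at 0.0167 is 81.5%. The minimum N is 44, or 45 with equal groups. At ρ = 0.4 the answer would be 54, and at 0.6 it would be 36. The stated 45 reproduces, and it points to ρ = 0.5.

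**2. Group main effect.** For a sustained effect d, the mean over three visits is (0 + d + d)/3 = 2d/3. The SD of that mean is √((1+2ρ)/3), so for d = 0.8 the standardised effect is:
- ρ = 0.3: 0.533/0.730 = 0.73
- ρ = 0.5: 0.533/0.816 = 0.65
- ρ = 0.7: 0.533/0.894 = 0.60

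All are below the 0.8 available at a single follow-up visit. In simulation (three arms of 15, sustained effects 0.8/0.4/0 SD, alpha 0.05) the main-effect test has about 40%, 32–33% and 26–27% power.

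**3. Variance at one visit.** The unadjusted difference has variance 2σ²/n. Adjusted for baseline it is 2σ²(1−ρ²)/n, a reduction of ρ²: 9%, 25% and 49%. Interval width scales with √(1−ρ²) = 0.95, 0.87 and 0.71.

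**4. Power at one visit, IG 1 against IG 2.** Unadjusted noncentrality is 0.8 × √(15/2) = 2.19 on 28 df, giving 56%. Adjusted, it is 2.19/√(1−ρ²) = 2.30, 2.53 and 3.07 on 27 df, giving 60%, 68% and 84%. Simulation, which lets baseline differ by chance between arms, gives 58–61%, about 66% and 81–84%.

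| Setting (noncentral t) | Raw | Adjusted, ρ 0.3 | ρ 0.5 | ρ 0.7 |
|---|---|---|---|---|
| 15 per arm, 0.8 SD, alpha 0.05 | 56% | 60% | 68% | 84% |
| 18 per arm, 0.8 SD, alpha 0.05 | 65% | 69% | 77% | 90% |
| 15 per arm, 0.8 SD, alpha 0.0167 | 38% | 41% | 50% | 70% |
| 15 per arm, 0.5 SD, alpha 0.05 | 26% | 28% | 33% | 46% |

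**5. If the t-tests were meant on change scores.** The standardised effect is then d/√(2(1−ρ)). Power at 15 per arm and 0.8 SD is 43%, 56% and 78%, still below the adjusted analysis at each correlation.

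**6. Against the interaction test.** Three arms of 15, effects 0.8/0.4/0 SD, alpha 0.05, simulated:

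| | Interaction, 4 df | ANCOVA, first follow-up | ANCOVA, mean of both follow-ups |
|---|---|---|---|
| Sustained, ρ 0.5 | 48% | 57% | 76% |
| Sustained, ρ 0.7 | 73% | 75% | 89% |
| Gone by second follow-up, ρ 0.5 | 46–49% | as above | 24–25% |
| Gone by second follow-up, ρ 0.7 | 71% | as above | 33% |

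The first-follow-up ANCOVA does not depend on what happens later, so its figures carry over.

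**The case against.** **The interaction test already uses baseline.** It compares within-child change, the trial was sized for it, and the t-tests follow only if it is significant. This stands. A reader might infer that the stated 80% power is wrong or lost; step 1 shows that it is neither. But the differences reported after that test still come from comparisons that omit baseline.

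**The gain could be small.** This stands in part. At a correlation of 0.3 the per-visit gain is about 2 to 5 points. At 0.5, the value the sample size implies, it is 10 to 12 points.

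**Much larger gains could be claimed.** A reader might take the 76% and 89% for the mean of both follow-ups as the value of baseline adjustment. Much of that gain comes from pooling two visits under a constant effect. If the effect has gone by the second follow-up, pooling does worse than the planned interaction test.

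**Age.** A reader might infer that age was a stratification factor wrongly left out. The sentence on age categories is too vague: it may describe strata or simply class grouping. No gain can be computed from the article, and an analysis plan not shown may list covariates.

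**Missing data.** The need to impute before a repeated-measures ANOVA is not a defect, since multiple imputation and sensitivity analyses are planned.

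**The control group.** It is not randomised, so ANCOVA has no automatic advantage over change scores there: with systematic baseline differences the two estimate different quantities. This stands and limits the point to IG 1 against IG 2.

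**Conclusion.** The point holds as an avoidable loss of precision in the per-visit comparisons and the group main effect. For the randomised contrast with 15 per arm and an assumed 0.8 SD effect, per-visit power is about 56% as planned. With baseline adjustment it is about 58–61%, 66–68% or 81–84% at correlations of 0.3, 0.5 and 0.7. The size rests on a correlation and an effect that the article does not state; at 0.5 SD, power is low either way (26% against 28–46%). It does not make the planned analysis of the randomised contrast invalid or the sample size calculation irreproducible. Nor would adjustment remove selection bias from comparisons with the control group.

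**What to change.** In Statistical analysis:

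- Replace the group main effect and the raw per-visit comparisons with a linear mixed model on the two follow-up scores: group, visit, group-by-visit and baseline score, with correlated errors within child.
- Report the baseline-adjusted group difference at each visit with its confidence interval. Pool the two visits only if a sustained effect is assumed in advance.
- If the three-visit interaction stays as the overall test, keep it distinct from the new model's group-by-visit term, which tests only whether the effect differs between the two follow-ups.
- For the K-WISC-V, use ANCOVA of the single follow-up on baseline.
- Say what the age categories were for, and add age category to the model only if it was a randomisation stratum.
- Keep multiple imputation as planned, or as a sensitivity analysis to the mixed model.
- Name IG 1 against IG 2 as the randomised contrast and label every comparison with the control group non-randomised, adjusted or not.

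The cost is a change of wording and one or two degrees of freedom. No extra visit, measurement or participant is needed, and the planned software fits these models.

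### The non-parametric fallback contains no test of group-by-time or of between-group change, so a normality test decides which hypothesis is tested; the resulting bias concerns comparisons with the non-randomised control group

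*Protocol article*

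**What the plan says.** The Sample size section fixes the question the trial is powered for: "the statistical test was designated as ANOVA: repeated measures, within-between interaction". The Statistical analysis section tests time, group and their interaction by repeated-measures ANOVA, on condition that normality (Shapiro-Wilk) is satisfied. If it is not, the section changes method: "The Kruskal-Wallis test will be used for between-group comparisons at each time point, while the Friedman test will be applied for within-group repeated measures".

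Post-hoc testing has a condition attached: "If significant interaction effects are observed in the repeated measures analysis, post-hoc tests will be conducted". The non-parametric post-hoc tests are then named. Between groups, "the Mann-Whitney U test will be used to compare two groups at a specific time point"; within a group, the Wilcoxon signed-rank test compares two time points.

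The Study design section randomises children to the two intervention groups. It fills the control group from families who cannot attend the interventions but can complete the assessments.

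**The concern.** The two branches answer different questions. The ANOVA asks whether the groups change differently over time. In the fallback, Kruskal-Wallis and Mann-Whitney ask whether raw scores differ between groups at one visit, and Friedman and Wilcoxon ask whether scores change within one group. None of the four compares change between groups, so an outcome that fails the normality check is never tested on the hypothesis that set the sample size.

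This matters most against control. That group is not randomised, so equal baselines are not expected by design. A raw-score test after the intervention carries any standing difference with it. It can report a group difference where the intervention did nothing, or miss a real improvement in groups that started worse.

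**Working it through.** **1. The plan's own figure.** Inputs from the Sample size section: effect size f ("was set to 0.25, based on previous studies [27–29"); significance level ("adjusting the per-comparison significance level to α = 0.0167"); and "The statistical power (1-β) was set at 0.80, the number of groups at three, and the number of repeated measurements at three". The correlation ρ between repeated measures and the sphericity factor are not given. I assume ρ = 0.5 and sphericity.

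- Noncentrality: λ = f² × N × m / (1 − ρ) = 0.0625 × 45 × 3 / 0.5 = 16.875
- Degrees of freedom: (3 − 1)(3 − 1) = 4 and (45 − 3)(3 − 1) = 84
- Power at α = 0.0167: 0.815, and 45 is the smallest multiple of three that reaches 0.80

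This reproduces the stated result: "the required sample size was recalculated to be 45 participants (15 per group". For ρ = 0.3, 0.5, 0.6 and 0.7 the total would be 63, 45, 36 and 30. The power belongs to the interaction test and does not carry over to the fallback tests.

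**2. What each named test compares.**

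| Test | Branch | Compares change between groups? |
|---|---|---|
| ANOVA interaction | normal | yes |
| Kruskal-Wallis at a visit | non-normal | no, raw scores at one visit |
| Mann-Whitney at a visit | non-normal | no, raw scores at one visit |
| Friedman | non-normal | no, one group over time |
| Wilcoxon signed-rank | non-normal | no, one group, two visits |

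**3. False positives against control.** Simulation: three groups of 18 (the planned size), α = 0.05, no intervention effect, and the control group shifted by the same amount at every visit. The correlation of 0.5 and the shifts are assumptions.

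| Control shift (SD) | 0 | 0.3 | 0.5 | 0.8 |
|---|---|---|---|---|
| Kruskal-Wallis, post visit | 5% | 12% | 28% | 64% |
| Kruskal-Wallis, change from baseline | about 5% | about 5% | about 5% | about 5% |
| Baseline as covariate (ANCOVA) | 5% | 7% | 13% | 24% |
| Mann-Whitney, IG 1 v IG 2, post visit | 4–5% | 4–5% | 4–5% | 4–5% |

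With skewed (lognormal) data and 2,000 runs per setting, the post-visit Kruskal-Wallis rejects 27% and 65% at shifts of 0.5 and 0.8 SD with ρ = 0.5, and 29% and 64% with ρ = 0.7.

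The covariate row has a simple explanation. With ρ = 0.5, adjustment removes ρ × shift and leaves (1 − 0.5) × shift, which is half of a persistent gap.

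**4. Missed effects.** Same lognormal set-up. Both intervention groups start 0.6 SD worse and truly improve by 0.6 SD. Post-visit Kruskal-Wallis rejects 4% of the time at either ρ. On change from baseline it rejects 39% (ρ = 0.5) or 60% (ρ = 0.7).

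**5. Limit of the change score.** The flat 5% in step 3 depends on a parallel shift. If half of the baseline gap closes by follow-up with no effect, Kruskal-Wallis on change rejects about 6%, 10% and 19% at gaps of 0.3, 0.5 and 0.8 SD.

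**The case against.** Several points on the other side stand and limit the finding.

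- **Randomised comparison.** A reader might infer that every non-normal outcome gives an invalid result. The documents do not support that. IG 1 and IG 2 are randomised, so a Mann-Whitney test at follow-up is a valid test of their difference (4–5% rejection under no effect at every setting). What it loses is the information in baseline.
- **Use of baseline.** It would be too strong to say that the fallback ignores baseline. Kruskal-Wallis is run at every visit, the first included, so a standing gap would be visible. Friedman and Wilcoxon use baseline within a group. Even so, no between-group test in this branch takes baseline into account.
- **The post-hoc trigger.** A reader might infer that non-parametric post-hoc tests can never be run. The condition can also be read as applying to the ANOVA branch only, which would leave the non-parametric follow-ups without a gate. On either reading the text does not say when they are run.
- **Within-group significance.** The plan nowhere says that arms will be compared by one being significant and another not, so that misuse cannot be attributed to it.
- **Parametric branch.** The parametric post-hoc t-tests between groups are also made at single visits, with the same exposure to a baseline gap. There, however, an interaction test comes first.
- **A conditional branch.** The ANOVA applies whenever normality holds. How often the fallback is entered cannot be judged from the article, which gives no score distributions and does not say whether Shapiro-Wilk is run on raw scores, by cell or on residuals.

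The largest point is that the inflation arises from the non-randomised control group. That is so. The fallback is what turns the gap into a reported group difference, and no analysis choice removes the underlying problem.

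**Conclusion.** The point holds in this form. The non-normal branch has no test of group-by-time or of between-group change, although the sample size rests on that interaction. A Shapiro-Wilk result thus selects the hypothesis, and the post-hoc condition has no equivalent in that branch. This follows from the text alone.

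The size of the harm rests on assumptions. It applies to comparisons with control and needs a baseline gap. With correlation 0.5 and a parallel gap of 0.3 to 0.8 SD, the false-positive rate at the post-intervention visit is about 12% to 64% instead of 5%. With no gap it stays at 5%.

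A reader might also infer that covariate adjustment for baseline, or the use of change scores, makes the control comparison sound. Neither does: the first leaves about 7% to 24% over the same gaps, and the second relies on the gap otherwise persisting.

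**What to change.** Rewrite the non-normal branch so that it keeps the group-by-time question:

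1. Judge normality on the residuals of the repeated-measures model.
2. If it fails, use one of two pre-named options. Either run Kruskal-Wallis and then Mann-Whitney on change from baseline at each follow-up, or run a rank-based, permutation or bootstrap test of the group-by-time interaction with baseline kept as a repeated measure.
3. Make the post-hoc tests in this branch conditional on that result.
4. Report Friedman and Wilcoxon results descriptively only.
5. Do not present covariate adjustment for baseline as a cure for the control comparison. State that change scores assume the baseline gap would otherwise have persisted, and that neither method repairs the non-randomised allocation.

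Cost: analysis wording and minor programming. No new data are needed.

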### Outcome measures

The final analysis will include data collected from a total of 54 children and their primary caregivers, with 18 children and their respective primary caregivers assigned to each of the two intervention groups and the control group: Intervention Group 1 (n = 36: 18 children, 18 parents), Intervention Group 2 (n = 36: 18 children, 18 parents), and the Control Group (n = 36: 18 children, 18 parents). Data from children and their primary caregivers will be analyzed separately.

The examiner will conduct the assessments while being blinded to the group assignment. Cognitive assessments will be administered by a certified clinical psychologist to quantitatively evaluate participants’ cognitive functions. Additionally, the physical activity level will be collected using the ActiGraph, and this data will be used to monitor the provided level of physical activity. The following assessment tools will be used for children with ADHD and their parents. For cognitive assessment, the Korean-Wechsler Intelligence Scale for Children, Fifth Edition (K-WISC-V) and the Visual-Motor Integration, Sixth Edition (VMI-6) will be used. For emotional assessment, the Revised Children’s Manifest Anxiety Scale (RCMAS) and the Children’s Depression Inventory (CDI) will be utilized. For behavioral assessment, physical activity levels will be measured using the Global Physical Activity Questionnaire (GPAQ). ADHD symptoms, social skills, and sleep quality will be evaluated using the Swanson, Nolan, and Pelham Questionnaire (SNAP), the Social Skills Rating System-Parent (SSRS-P), and the Korean Version of the Pittsburgh Sleep Quality Index (PSQI-K).

For primary caregivers, the assessment tools will include the GPAQ, the Parenting Stress Index-Short Form (PSI-SF), the Beck Anxiety Inventory (BAI), the Beck Depression Inventory (BDI), and the Korean Version of the Pittsburgh Sleep Quality Index (K-PSQI).

All groups will undergo three assessments for all measures except for the K-WISC-V. Intervention Groups 1 and 2 will be assessed before the intervention, immediately after the intervention (three months after the first assessment), and three months post-intervention. The control group will be assessed at baseline, after three months, and after six months. The K-WISC-V will be administered to all groups before the intervention and six months post-intervention. Detailed information about the outcome measures can be found in Table 3.

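### The follow-up to a significant interaction contains no pairwise contrast of change and no firm multiplicity rule, so it cannot validly say which arms differ in change

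*Protocol article*

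**What the plan says.** The trial has three arms. Sample size sets "the number of groups at three, and the number of repeated measurements at three", and Outcome measures confirms that "All groups will undergo three assessments for all measures except for the K-WISC-V".

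Statistical analysis makes the follow-up conditional: "If significant interaction effects are observed in the repeated measures analysis, post-hoc tests will be conducted". The parametric follow-up is then listed: "paired t-tests will be used to compare within-group differences over time, and independent t-tests will be performed to compare mean differences between groups". Each of these between-group comparisons is made within a single visit. Wilcoxon signed-rank and Mann-Whitney tests are the non-parametric versions.

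On multiplicity, the section states that "Bonferroni correction will be applied as needed to control for Type I error", without a family or a divisor. It later fixes 0.0167 for the Wechsler scores and adds: "For other variables, the significance level will be set to 0.05 for analysis". Sample size, by contrast, uses 0.0167 per comparison for the trial as a whole.

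Under Study design, the two intervention groups are filled by random assignment. The control group is drawn from families who cannot attend the interventions but can complete the assessments.

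**The concern.** An interaction means that change over time differs somewhere among the three arms. The natural next question is which pair of arms differs in change, and by how much. None of the listed follow-up tests answers it. A paired test uses one arm only. A same-visit t-test compares raw means and ignores where each arm started.

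Two conclusions are at stake.

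- Significant improvement in one arm but not in another is easily read as a difference between them. Retest gains, maturation and regression to the mean all produce within-arm change, and with 18 per arm, chance decides which arms cross the threshold.
- A gap between control and an intervention group that was present at baseline can reappear at follow-up as an apparent effect.

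With a discretionary correction and a stated level of 0.05, nothing in the text limits the number of false pairwise statements once the gate has opened.

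**Working it through.** **The plan's own figure.** Sample size gives 45 participants (f = 0.25, α = 0.0167, power 0.80, 3 groups, 3 measurements). Assuming the two unstated inputs (correlation 0.5, ε = 1):

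- λ = f²·N·m/(1 − ρ) = 0.0625 × 45 × 3 / 0.5 = 16.875
- df = (3 − 1)(3 − 1) = 4 and (45 − 3)(3 − 1) = 84
- power = 0.8145

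So 45 reproduces, at 0.0167 and for the omnibus interaction.

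**Counting the follow-up tests, per three-visit outcome.**

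- Within arm: 3 arms × 3 visit pairs = 9
- Between arms: 3 arm pairs × 3 visits = 9, of which 3 are at baseline
- Total 18, none of them a contrast of change between two arms

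Wechsler scores are different: "The K-WISC-V will be administered to all groups before the intervention and six months post-intervention". Two visits give 3 + 6 = 9 tests per score.

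**False positives under the listed procedure.** Simulation, 20,000 trials: 18 per arm, three visits, equal visit correlation 0.5 (assumed), interaction test at 0.05 as the gate, then the 18 tests. A false positive is a rejection of a comparison whose true difference is zero.

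| True situation | Level | At least one false positive, gate applied |
|---|---|---|
| No arm differs | 0.05 | about 5% |
| Only group 1 changes, 0.8 SD | 0.05 | about 30% |
| Same | 0.0167 | about 13% |
| Only group 1 changes, 1.5 SD | 0.05 | about 39% |
| Same | 0.0167 | about 16% |

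The percentages are of all trials. When only group 1 changes, 12 of the 18 comparisons are truly null: 7 within arm and 5 between arms. With correlation 0.7 the 0.8 SD rows become 36% and 15%.

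**Within-arm tests as evidence.** Let all arms drift by 0.5 SD and group 1 gain a further 0.8 SD. Group 2 and control are then identical. With correlation 0.5 the SD of change is 1, and a paired t-test with n = 18 has power 0.516. Two identical arms therefore disagree with probability 2 × 0.516 × 0.484 = 0.50 before the gate. Among simulated trials that pass the gate, the figure is about 53% (33% with a 0.3 SD drift).

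**Raw same-visit tests against control.** Let control differ from the others by a constant 0.5 SD, with no change in group 2 or control, while group 1 changes by 0.8 SD. Among trials that pass the gate, the raw group 2 versus control test at a follow-up visit rejects in about 31%. A contrast of change rejects in about 7%.

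**Non-parametric route.** Kruskal-Wallis compares arms at one visit, and Friedman compares visits within an arm. Neither tests an interaction, so the stated condition for post-hoc testing cannot be evaluated there.

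**Replacement contrasts.** Three pairs × two follow-up visits = 6 contrasts of change. At 0.05/6 = 0.0083, without any gate, the chance of any false positive is about 4.5% when nothing differs and 1.7% when only group 1 changes. At 0.0167 the same six contrasts give about 8% when nothing differs, so 0.0167 fits only three contrasts.

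**The case against.** The strongest defence is the gate. With no true difference, the 18 tests would yield at least one p < 0.05 in about 48% of trials if run unconditionally, but in about 5% once a significant interaction is required. Likewise, if all arms drift equally by 0.5 SD, the three arms give discordant within-arm results in about 75% of trials without the gate and under 5% with it. A reader might infer the larger figures from the list of tests. They do not describe the parametric plan. Nor should one assume 18 × 12 = 216 tests across the twelve non-Wechsler outcomes, since that requires an interaction in every one.

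A reader might also infer that no test compares the arms. That is wrong: the interaction compares change across all three, and the independent t-tests compare arms directly. For group 1 versus group 2, which are randomised, the raw follow-up difference is unbiased, if less precise than a baseline-adjusted one.

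Finally, the Bonferroni sentence stands next to the post-hoc sentence, and 0.0167 matches three arm pairs, so correction may be intended and 0.05 may be the omnibus level. An analysis plan could settle the family. But the published text says otherwise for the non-Wechsler outcomes, and a divisor would not supply the missing contrast. What stands of the defence is that error is controlled when nothing differs. It does not protect the pairwise statements made after a real interaction.

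**Conclusion.** The point holds in limited form. The omnibus interaction is a legitimate test of differing change. The follow-up is not a valid way to attribute it to particular arms, and its level conflicts with the 0.0167 used for sizing.

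The inflation arises once an arm truly changes, which is when the follow-up will be read, and on the non-parametric route, where no gate is defined. The baseline-gap problem concerns comparisons with control and not group 1 versus group 2.

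The simulated sizes rest on 18 complete pairs per arm, equal visit correlations of 0.5 and normal data, and on effect, drift and gap sizes chosen for illustration. None of these is given in the article. The count of 18 tests and the absence of a pairwise change contrast rest on the text alone. This should be changed before analysis.

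**What to change.** - Replace the post-hoc list with the three pairwise between-arm contrasts of change from baseline, with confidence intervals.
- Name one follow-up visit as the main one and test at 0.05/3 = 0.0167, in line with Sample size. If both follow-up visits are tested, use 0.05/6 = 0.0083. State the rule without the discretionary wording, and for the non-Wechsler outcomes too.
- On the non-parametric route, apply rank tests to change scores.
- Baseline-adjusted contrasts may be used for group 1 versus group 2. For comparisons with control, use change from baseline and label them non-randomised. Adjustment does not remove a stable gap: at correlation 0.5, a 0.5 SD gap leaves 0.5 × (1 − 0.5) = 0.25 SD of spurious effect, and the adjusted contrast then rejects in about 12% of trials at 0.05, against 5% for change. Change in turn removes only a gap that is stable over time.
- Drop the baseline tests. Report within-arm change descriptively with confidence intervals, not as evidence of effect.

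The cost is analysis wording and slightly different model output, with no extra participants or data. The downside is fewer p-values and a stricter level for the non-Wechsler outcomes.
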